### Sample size {14}

The sample size calculation was based on:
A mean Comprehensive Complication Index (CCI) of 30±10 (mean±SD) in the control group, derived from a dataset of patients undergoing upper GI surgery in our department [25].A minimal clinically relevant reduction of the CCI by 6 with pre-habilitation, resulting in a CCI of 24±10 (Mean±SD).An alpha error of 0.05 (5 %) and a power of 0.9 (90 %) based on a two-sample *t* test to compare the two group means.A drop-out rate of 10 %.

The power was calculated for a range of total sample sizes, *n*_*i*=1,.,39_ = 10, ..., 200, using the R [26] package sse [27]. To assess the sensitivity of the sample size calculation with respect to the expected treatment effect, we used a range of effect sizes, θ, from 2 to 10.

Under the assumptions described above, 134 patients should be recruited for this study (67 per group), to ensure 120 evaluable patients considering a drop-out rate of 10 %. Figure 1 shows how the total sample size (both groups together, without drop-outs) depends on the expected effect size, θ.

**Fig. 1 Fig1:**
[figure not shown]
Sensitivity of the sample size with regard to the expected effect size, θ, given a within group standard deviation of 10. An example is shown for θ =6 and a power of 90 %. The curves are smoothed and shown for illustration only

### Recruitment {15}

Patients are screened by treating physicians in the outpatient clinic where the indication for elective abdominal surgery is made.

Patients are seen by a physical therapist in order to explain the training in a separate meeting.

## Assignment of interventions: allocation

### Sequence generation {16a}

Consecutively screened and eligible patients will be included in the trial. In order to achieve comparable study groups, patients will be allocated by randomization after given written informed consent using SecuTrial®, conducted at the Clinical Trial Centre (CTC), University of Zürich.

### Concealment mechanism {16b}

Randomization will be performed via variance minimization using the variables patient age and BMI, localization of disease (upper vs. lower gastro-intestinal, HPB, hernia, others) and disease dignity (benign vs. malign). To avoid allocation being fully deterministic, we will set the predictability to 80%.

### Implementation {16c}

The randomization is performed in a 1:1 ratio to either the intervention or the control arm of the study with SecuTrial® at the CTC at the University of Zürich.

Enrolling of patients will be performed by DB, KP or AM.

## Assignment of interventions: blinding

### Who will be blinded {17a}

The participants as well as the treating persons will not be blinded. The further treatment is not influenced by the preoperative respiratory training and study objectives are all objective measurements and not dependent on the treating physicians, as they are registered in the Power®Breathe KHP2 device. The outcome assessors are partially blinded and the analysis will be performed by a blinded statistician.

### Procedure for unblinding if needed {17b}

The design is open label with outcome assessors being partially blinded and a blinded data analyst so unblinding will not occur.

## Data collection and management

### Plans for assessment and collection of outcomes {18a}

The following documents are considered source data, including but not limited to:
The main source of information is our clinic information system.SAE worksheets.Nurse records, records of clinical coordinators and physiotherapists.Medical records from other department(s), or other hospital(s), or discharge letters and correspondence with other departments/hospitals, if the participant visited any during the study period and the post-study period.

The investigators will use electronic case report forms (eCRF) of SecuTrial®, one for each enrolled study participant, to be filled in with all relevant data pertaining to the participant during the study. All participants who either entered the study or were considered not eligible or were eligible but not enrolled into the study additionally must be documented on a screening log. The investigator will document the participation of each study participant on the enrolment Log.

### Plans to promote participant retention and complete follow-up {18b}

Patients are encouraged to adhere to the training program as well as to perform physical activity besides the inspiratory training. Correspondingly, healthcare professionals are able to review patient progress by tracking up to 36 training sessions, which the KHP2 can store. Clinical research has shown high patient motivation due to the on-screen feedback which has resulted in high compliance (90%+) and significantly improved lung muscle strength and stamina.

### Data management {19}

For data and query management, monitoring, reporting and coding an internet-based secure data base SecuTrial® developed in agreement to the Good Clinical Practice (GCP) guidelines provided by the (CTC) Zurich will be used for this study. It is the responsibility of the investigator to assure that all data during the study will be entered completely and correctly in the respective database. Corrections in the eCRF may only be done by the investigator or by other authorized persons. In case of corrections, the original data entries will be archived in the system and can be made visible. For all data entries and corrections date, time of day and person who is performing the entries will be generated automatically.

The trial master file present at the University Hospital of Zürich will have all requested original data filed.

### Confidentiality {27}

It is assured that any authorized person, who may perform data entries and changes in the eCRF, can be identified. A list with signatures and initials of all authorized persons will be filed in the study site file and the trial master file, respectively.

Documented medical histories and narrative statements relative to the participants’ progress during the study will be maintained in the clinical information system. These records will also include the following: originals or copies of laboratory and other medical test results (e.g. ECGs, etc.) which must be kept on file with the individual participant’s *eCRF*.

The investigators assure to perform a complete and accurate documentation of the participant data in the eCRF. All data entered in the eCRF must also be available in the individual participant file either as printouts or as notes taken by either the investigator or another responsible person assigned by the investigator.

Essential documents must be retained for at least 10 years after the regular end or a premature termination of the respective study (KlinV Art. 45). Essential documents must be retained according to local law in the case of international multicentre studies.

Direct access to source documents will be permitted for purposes of monitoring, audits and inspections.

### Plans for collection, laboratory evaluation and storage of biological specimens for genetic or molecular analysis in this trial/future use {33}

All study data will be archived for 10 years after study termination or premature termination of the clinical trial. On the consent form, participants will be asked if they agree to use of their data should they choose to withdraw from the trial. Participants will also be asked for permission for the research team to share relevant data with people from the Universities taking part in the research or from regulatory authorities, where relevant. This trial does not involve collecting biological specimens for storage.

The length of stay (LOS) will be analysed as time to hospital discharge alive, using a Cox proportional hazards model. If there are patients who died during the hospital stay, in-hospital death will be considered as competing risk and patients will be censored at the date of death in a cause-specific Cox proportional hazards model. The binary outcomes readmission and mortality within 90 days will be compared with a logistic regression model. MIP, Load, Energy, Power, Volume and the sit-to-stand test results, which are measured multiple times per patient, will be compared with linear mixed-effects models with a random intercept per patient to account for the non-independence of repeated measurements on the same patient. Treatment will be used as explanatory factor with age, BMI, disease localization and disease dignity as covariates in the statistical models as in the analysis of the primary outcome. In addition, time of measurement and the interaction of time and treatment will be included in the mixed-effects models. Secondary outcomes will be evaluated using complete case analysis applied to the FAS.

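### The fully adjusted logistic model for 90-day mortality has no finite maximum-likelihood solution at the two or so deaths that the plan's own CCI assumptions allow (minor)

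*Protocol article*

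**What the plan says.** Statistical methods for primary and secondary outcomes {20a} states: "The binary outcomes readmission and mortality within 90 days will be compared with a logistic regression model". Later in the same paragraph it adds: "Treatment will be used as explanatory factor with age, BMI, disease localization and disease dignity as covariates in the statistical models", in line with the primary analysis. The sentence after that adds time and its interaction with treatment for the mixed-effects models only, so the covariate rule is most naturally read as covering the logistic models too.

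Concealment mechanism {16b} gives the categories: "localization of disease (upper vs. lower gastro-intestinal, HPB, hernia, others) and disease dignity (benign vs. malign". Localization therefore has five levels.

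Sample size {14} rests on "A mean Comprehensive Complication Index (CCI) of 30±10 (mean±SD) in the control group" and "A minimal clinically relevant reduction of the CCI by 6 with pre-habilitation, resulting in a CCI of 24±10 (Mean±SD", and concludes that "134 patients should be recruited for this study (67 per group), to ensure 120 evaluable patients considering a drop-out rate of 10" per cent. Outcomes {12} lists mortality during 90 days as a secondary endpoint and scores a death as 100 on the CCI.

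No mortality rate is given. The length-of-stay analysis makes conditional provision for in-hospital deaths; the mortality model has no provision for sparse events.

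**The concern.** A logistic model needs deaths and survivors spread across its covariate levels. If one localization level has no deaths, its coefficient runs to minus infinity and the full model has no finite maximum-likelihood solution. If all deaths fall in one arm, the treatment odds ratio itself goes to zero or infinity.

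The trial is sized for a difference in mean CCI, not for mortality, and its planning figures imply very few deaths. The model named for this endpoint may then fail to return what it is meant to deliver, and the replacement would have to be chosen once the deaths have been counted.

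**Working it through.** **1. The plan's sample size.** Inputs from Sample size {14}: difference 6, SD 10, "An alpha error of 0.05 (5 %) and a power of 0.9 (90 %) based on a two-sample" t test, taken as two-sided. The normal approximation gives n per arm = 2 × (1.960 + 1.282)² × 10² / 6² = 58.4, so 59. The exact noncentral t gives power 0.898 at 59 and 0.903 at 60 per arm, hence 120 evaluable. Dropout: 120 / 0.9 = 133.3, so 134. The plan's figures reproduce.

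**2. Parameters in the mortality model.** Intercept 1, treatment 1, age 1, BMI 1, localization 5 − 1 = 4, dignity 1: nine in all, eight of them slopes (age and BMI taken as linear).

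**3. Mortality ceiling from the plan's own inputs.** With death = 100, Cantelli's inequality gives P(death) ≤ SD² / (SD² + (100 − mean)²).
- Control: 100 / (100 + 70²) = 100 / 5000 = 2.0%.
- Intervention: 100 / (100 + 76²) = 100 / 5876 = 1.7%.

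The ceiling is reached only if every survivor in an arm has the same CCI, so any spread among survivors pushes it lower.

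Expected deaths at the ceiling: 60 × 0.0200 + 60 × 0.0170 = 2.2 in 120 patients, or 67 × 0.0200 + 67 × 0.0170 = 2.5 in 134. From the binomial distributions, P(4 or fewer deaths) is 0.93 with 120 and 0.90 with 134.

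**4. The full model.** Four or fewer deaths cannot cover five levels, so at least one enrolled level has none and no finite solution exists. This needs no simulation. With deaths placed at random among 120 patients (assumed localization shares 25/25/30/10/10%), a linear-programming check for separation found no finite solution in 99% of data sets with 5 deaths, 93% with 6, 78% with 8 and 72% with 10.

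**5. The treatment odds ratio.** This is the quantity of interest, and it fails less often than the full model. A direct check at 2% mortality with 60 per arm: P(at least one arm has no deaths) = 2 × 0.98⁶⁰ − 0.98¹²⁰ = 0.51.

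Simulated trials with N = 120 gave the results below. The ranges cover different assumed case mixes (equal shares; 25/25/30/10/10%; shares of 15 to 25%). A trial with no deaths counts as undefined.

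| Assumed mortality | Expected deaths | Some coefficient not finite | Treatment odds ratio infinite or undefined |
|---|---|---|---|
| 2% | 2.4 | 99-100% | 52-57% |
| 3% | 3.6 | 98-100% | 29-33% |
| 5% | 6.0 | 85-98% | 5-10% |

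With 134 patients and two of these case mixes, the treatment odds ratio fails in 27-28% of trials at 3% mortality and about 7% at 5%.

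**6. Information when the odds ratio is finite.** Events per slope are 1.2 / 8 = 0.15 at 1% mortality and 6.0 / 8 = 0.75 at 5%.

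**The case against.** **The failure rates near 100% are not failure rates of the treatment estimate.** A reader might infer from the third column of the table that the plan almost never yields a usable mortality odds ratio. The documents do not support that. The column counts divergence of any coefficient, including that of a localization level without deaths; in such a trial the treatment odds ratio can remain finite, though imprecise. This objection stands, and the last column is the relevant one.

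**The 2% ceiling is conditional.** It takes 30±10 as true of this trial, whereas Sample size {14} draws that value from upper GI patients and the trial also enrols lower GI, HPB, hernia and other cases. This also stands: actual mortality could differ, and no rate is stated. At 10% mortality some coefficient fails in 41% to 83% of simulated trials, depending on the case mix, and the treatment odds ratio in fewer than 1% (two of the case mixes).

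**The estimator is not named.** Firth-penalised logistic regression is also a logistic regression, and an analysis plan not shown might specify it. This lowers the weight of the point but does not remove it. Without qualification, the named model is ordinarily fitted by maximum likelihood, and that fit fails on the data the plan expects.

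**A choice made with knowledge of allocation.** A reader might fear this, but Who will be blinded {17a} provides for a blinded statistician. What remains is a choice made after the deaths are known.

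**No method would be informative.** With two deaths, both in one arm of 60, Fisher's exact test gives p = 2 × 1770 / 7140 = 0.50; p < 0.05 needs six against none. This is true, but it favours a plain descriptive comparison over a nine-parameter model.

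**Readmission and grade ≥3b.** A reader might extend the point to these outcomes. The document gives no rates for them, and at 20% incidence only 4% of simulated trials had any non-finite coefficient (case mix of 15 to 25% shares). No defect is shown there.

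**Conclusion.** The point holds, as a minor one. If the plan's CCI assumptions hold, mortality is at most about 2%, or roughly two deaths in 120 patients, and the fully adjusted model then very probably has no finite maximum-likelihood solution; with four or fewer deaths and all five localization levels enrolled this is certain. The treatment odds ratio itself would be infinite or undefined in roughly 50-57% of trials at 2% mortality, about 30% at 3% and 5-10% at 5%. In the remaining trials it may be finite but rests on very few events.

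The ceiling follows from the stated means and SDs. The individual mortality rates, the case mix and the strength of the risk factors in the simulations are assumptions. It would be too strong to say that the plan cannot yield any mortality estimate. Mortality is a secondary outcome, and the primary CCI analysis is unaffected.

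**What to change.** For 90-day mortality only, replace the fully adjusted maximum-likelihood model with one of the following:

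- Counts per arm and the risk difference with a score or exact 95% confidence interval, adding Fisher's exact test if a p-value is wanted. The cost is a mortality comparison without covariate adjustment.
- Firth-penalised logistic regression with treatment and the minimisation covariates, if adjustment is to be kept. The estimates are then finite, but they still rest on the same few deaths.

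The choice should be written down before the outcome data are examined. It is a change of wording only, with no effect on sample size or data collection. The readmission and grade ≥3b analyses can stay as they are.

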## Introduction

### Background and rationale {6a}

Postoperative pulmonary complications are frequent and have a significant impact on patient morbidity and mortality. These complications are particularly common after major abdominal procedures and can be considerable. The connection is likely that major abdominal surgery temporarily reduces respiratory function due to reduction of diaphragmatic strength caused by pain, anaesthesia and inhibitory reflexes as a consequence of splanchnic organ manipulation [1]. This reduction may be adequate to lead to complications or to not be able to ward off infections sufficiently. Pulmonary complications increase not only the length of hospital stay, medical consumption, thus suffering and costs [2–4], they are also the main reason for readmissions to critical care units after major surgery [5].

Inspiratory training is a cornerstone of postoperative physiotherapy and has been performed routinely for a long time [6]. The purpose of all inspiratory muscle training in any exercise regimen is to strengthen the muscles and increase breathing volume, thus leading to better physiological reserve. By inspiring against individual resistance, the muscles progressively strengthen by regular training, which may result in improved respiratory capacity [7]. In order to improve the reserves even before an operation—in the consideration of being more resistant with better reserves—physiotherapeutic regimes and studies are increasingly shifting from post- to preoperative [8, 9].

Most studies consist of multiple-component structured programs [10] including nutritional adaptations, high-intensity interval training, and supervised training sessions [11, 12]. The training span of different prehabilitation regimens is wide with a range from one to 6 weeks [13, 14]. However, implementation in clinical practice of these complex training schedules is hardly possible.

While systematic reviews have shown an advantage of these multi-step concepts regarding hospital length of stay, studies evaluating exclusively specific respiratory components are scarce [15, 16].

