### Trial design {8}

This is a prospective randomized-controlled single-centre open-label trial with a 1:1 allocation. The framework of the study is designed to test the superiority of preoperative inspiratory muscle training on postoperative complications in abdominal surgery.

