(LOAD) is a measure of resistance to inhalation, and represents the pressure generated in the airways due to the force of the inspiratory muscles during a training session. As the training load decays with increasing lung volume (in order to match the length-tension characteristics of the inspiratory muscles), the load displayed corresponds to the resistance at the start of inhalation (i.e. at RV). A higher load result means that the patient is training their inspiratory muscles harder, leading to stronger muscles. Stronger inspiratory muscles will need to work less hard to cope with the demands of breathing, leading to reduced breathlessness [cmH20].

(POWER) is a measure of muscle performance which combines strength and speed of movement (pressure × flow). More powerful muscles will be more resistant to fatigue at a given level of work and therefore, breathlessness will be reduced. The value displayed is the average power for all breaths in a training session.

(Breathing Energy) is a measure of the mechanical work (or effort) of breathing during your breathing training session. It is a result which combines the force exerted by your inspiratory muscles and the volume (1) of air inhaled. The higher the value of breathing energy you attain, the longer and harder you have worked your inspiratory muscles.

During the sit-to-stand test, the quantity [n] how often a patient can sit down on a chair and stand up during 60 s is noted. These values are evaluated at admission to hospital for surgery and 5 days after surgery.

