## Participant timeline {13}

The participant timeline is shown in Table 1.

**Table 1 Tab1:** Participant timeline

***Visit***	***1***	***2***	***3***	***4***		***6***	***7***	***8***
*Time (day)*		***0***	***7 +/-2d*** ^***a***^	***14 +/-4d***	*0*	***5+/-2d pod***	***x pod***	***90+/-14 pod***
*Patient schedule*	***Screening visit***	***Baseline visit***	***Compliance visit***^a^	***Admission to hospital***	***Surgery***	***Day 5 after surgery***	***End of hospitalisation***	***End of study visit***
*Hospital status*	*Outpatient*				*Inpatient*			*Outpatient clinic*
*Patient information and informed consent*	*x*							
*Demographics*	*x*							
*Medical history*	*x*			*x*				
*Medication*^b^	*x*			*x*			*x*	
*In-/exclusion criteria*	*x*	*x*						
*Administer medical device and training instruction*		*x*						
*Inspiratory muscle training (IMT)*		x	*x*	*x*				
*Power®Breathe device*		*KHP2*^*c*^*,KH2*	*KHP2*	*KHP2*^d^		*KH2*		
*Compliance check and training performance*			*x*					
*VAS/NRS/ Vital signs*				*x*		*x*	*x*	
*BMI*	*x*			*x*				
*Maximum inspiratory pressure*		*x*		*x*		*x*		
*Load (cmH20), Power (Watt), Breathing Energy (Joule), Volume (l)[measured by Power®Breathe device*]		*x*	*x*	*x*		*x*		
*Sit-to-stand test*		*x*		*x*		*x*		
*(Serious) Adverse events*		*x*	*x*	*x*		*x*	*x*	*x*
*Complications*							*x*	*x*

^a^When IMT (inspiratory muscle training) > 15 days, patients are offered an additional appointment with physio on demand, scheduled training can be extended up to 6 weeks

^b^Antibiotics, immunosuppressants, anticoagulants, insulin, oral antidiabetics

^c^Hand out Power®Breathe KHP2 device by a physiotherapist to patient

^d^Return of Power®Breathe KHP2 device to the physiotherapist on the ward

*pod* postoperative day, *VAS* visual analogue scale, *NRS* numerical rating scale, *BMI* body mass index

Control group starts at Visit4: hospital admission. The postoperative procedure is the same for both groups

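### The random-intercept models for the physiotherapy measures assume equal variance at admission and on day 5; if spread changes with surgery, the arm differences at those visits get miscalibrated standard errors (minor)

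*Protocol article*

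**What the plan says.** Statistical methods {20a} states that the repeatedly measured physiotherapy outcomes "will be compared with linear mixed-effects models with a random intercept per patient to account for the non-independence of repeated measurements". Treatment and the minimization variables are fixed effects, and "time of measurement and the interaction of time and treatment will be included in the mixed-effects models". The section names no visit-specific residual variance, unstructured covariance or robust standard error. It does not say which contrast will be reported. It adds: "Secondary outcomes will be evaluated using complete case analysis applied to the FAS".

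On timing, Outcomes {12} says: "These values are evaluated at admission to hospital for surgery and 5 days after surgery". Table 1 (Participant timeline {13}) also lists MIP, the device measures and sit-to-stand at the baseline visit, and the device measures at the compliance visit. Its footnote, however, reads "Control group starts at Visit4: hospital admission". The visits that both arms share are therefore admission and day 5.

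Background {6a} describes what happens between them: "major abdominal surgery temporarily reduces respiratory function due to reduction of diaphragmatic strength caused by pain".

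**The concern.** In its ordinary meaning, a random intercept with a homogeneous residual is compound symmetry: one variance at every visit and one correlation for every pair of visits. Here the two shared visits lie either side of a major operation. The patients range from hernia to upper gastro-intestinal and HPB surgery, so the loss of function may well differ between them. Equal spread before and after surgery is possible, but nothing in the protocol supports assuming it.

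Two questions of interest are visit-specific. The first is whether trained patients were stronger when they came to surgery, and the second is whether they were stronger on day 5. Controls are first measured at admission, so the first question can be compared between arms only through the admission difference. The interaction over the two shared visits answers something else, namely whether the arms differ in perioperative change. If the variances differ, both visit-specific differences carry standard errors built from a pooled variance that fits neither visit.

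**Working it through.** **The plan's own figure.** The only sample-size figures concern the CCI: a difference of 6, SD 10, and "An alpha error of 0.05 (5 %) and a power of 0.9 (90 %) based on a two-sample" *t* test. Taken as two-sided (the article does not say), the calculation gives 59.35, so 60 per arm and 120 evaluable, with power 0.903. Then 120 / 0.9 = 133.3, so 134. The stated total reproduces. It does not bear on this point, except that it supplies about 60 patients per arm under 1:1 allocation.

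**Inputs for the check.** Two shared visits, 60 complete cases per arm, nominal two-sided 5%. Let s1 and s2 be the SDs at admission and on day 5 after covariate adjustment, c their covariance, and r = s2/s1. No SD or correlation for these outcomes appears in the documents, so r is an assumption and is shown over a range.

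**Visit-specific difference.** With complete pairs, the model's common variance is v = (s1² + s2²)/2.

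- Model SE at either visit: √(2v/60)
- True SE at visit j: √(2sj²/60)
- Ratio of model to true SE: √v / sj
- Actual type I error: 2[1 − Φ(1.96 × ratio)]

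The 60 cancels, so a larger trial would not remove the error. Worked example with s1 = 1 and r = 0.8: v = (1 + 0.64)/2 = 0.82 and √v = 0.906. At admission the ratio is 0.906, and 1.96 × 0.906 = 1.775, giving 7.6%. On day 5 the ratio is 0.906/0.8 = 1.132, and 1.96 × 1.132 = 2.219, giving 2.7%.

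| Assumed r | Admission: SE ratio | Admission: type I | Day 5: SE ratio | Day 5: type I |
|---|---|---|---|---|
| 0.6 | 0.825 | 10.6% | 1.374 | 0.7% |
| 0.8 | 0.906 | 7.6% | 1.132 | 2.7% |
| 0.9 | 0.951 | 6.2% | 1.057 | 3.8% |
| 1.0 | 1.000 | 5.0% | 1.000 | 5.0% |
| 1.1 | 1.051 | 3.9% | 0.956 | 6.1% |
| 1.25 | 1.132 | 2.7% | 0.906 | 7.6% |

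At the visit with the smaller variance the cost is power. Where a correct test would have 80%, a ratio of 0.8 or 1.25 leaves Φ(2.802 − 2.219) = Φ(0.583), or 72%.

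**Contrasts that are not affected.** The fitted correlation is c/v.

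- Change between visits: the model variance is 2v(1 − c/v) = s1² + s2² − 2c, which is the true variance.
- Average over visits: the model variance is v(1 + c/v)/2 = (s1² + s2² + 2c)/4, again the true variance.

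**Simulation check.** REML fits (4,000 runs per setting, within-patient correlation 0.4 and 0.7) agree with the closed form. At r = 0.8, type I error was 7.3–8.1% at admission and 2.9% on day 5. At r = 0.6 it was 10.8% and 0.9%. Over r = 0.6 to 1.25 the interaction kept an SE ratio of 0.99–1.01 and a type I error of 5.0–6.1%. Adding a baseline visit in the training arm only (with the same SD as admission) left the pattern in place: at r = 0.8, 6.7–6.9% at admission and 2.5–2.6% on day 5. The interaction then stayed close to valid, at 4.5–5.9%.

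**The case against.** The strongest reply is that the article describes a random effect, not a residual structure. A random intercept can be combined with visit-specific residual variances or robust standard errors, and an analysis plan that is not shown might specify either. That is fair, and it is why the point applies to the model as written, with the default residual. It does not remove the point, because the article names a particular model whose ordinary reading is compound symmetry, and a better choice can be stated at almost no cost.

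A reader might go further and infer that the standard errors are wrong as a matter of fact. The documents do not support this. They give no SD for any of these outcomes at any visit, and the statement in Background {6a} that surgery reduces respiratory function is about level, not spread. For ratios between 0.9 and 1.1 the standard errors are off by no more than about 6%.

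A reader might also infer that the whole physiotherapy analysis is compromised, or that the visit-specific differences are the declared target. Neither follows. Statistical methods {20a} does not name the contrast to be reported, and the secondary objective in Objectives {7} speaks loosely of physiotherapeutic changes, which could mean the interaction. That contrast remains valid over the two shared visits. What the objection does not answer is that the interaction cannot show whether training raised strength before surgery, because controls have no pre-training value.

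**Conclusion.** The point holds in conditional form and is minor. As written, with the default residual, the model assumes equal variance at admission and on day 5. If that assumption fails, the arm difference is tested too liberally at the visit with the larger spread and too conservatively at the other. The size rests wholly on the assumed SD ratio: nil at 1.0, small at 0.9 to 1.1, and 7.6% and 2.7% against a nominal 5% at 0.8 or 1.25, with larger departures beyond that. The figures also assume about 60 complete cases per arm and two shared visits.

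Only the secondary physiotherapy outcomes are touched. The interaction and the visit average over the two shared visits, the primary CCI analysis and the sample size all stand. The admission difference is the reason to act, since it is the only between-arm evidence on strength gained before surgery.

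**What to change.** For admission and day 5, the two visits both arms share, replace the random intercept by an unstructured covariance, that is, a separate variance at each visit and a free correlation. Keep the stated fixed effects, including time-by-treatment, and report the treatment difference with its confidence interval at admission and on day 5 from that model.

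The cost is a change of wording and one extra variance parameter (three covariance parameters instead of two), which about 120 patients can easily support. No new data are needed. If the variances turn out equal, the results will be essentially the same. Fixing the structure before the data are analysed also avoids choosing it after seeing them.
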